#### Participant screening

2.9.1

Trial data clerks and fieldworkers will screen women for eligibility at delivery at the maternity wards, post-natal clinics, child welfare clinics, female adult wards, gynaecology wards and outpatient clinics to allow capture of adverse pregnancy outcomes and early pregnancy losses. Trial fieldworkers will conduct home visits to screen eligible women who delivered at home or in non-study sites within the first 8 weeks post pregnancies. Trial data clerks will contact participants when the follow-up window opens (6–8 weeks post pregnancy) to minimise loss to follow-up.

### Sources of data

2.10

The primary data source will be the mother and child health book and the CHP case report form. Health facility registers will be the secondary source, and patient interviews, the tertiary source.

#### The MCH book

2.10.1

All mother and child health services including routine visits during and after pregnancy, visits due to illness and visits for vaccination are documented in the MCH book (also known as MoH 216 or the ANC book). These books are printed by the government and issued to each pregnant woman free of charge during their first ANC visit. Women are expected to carry them for every subsequent visit until their child attains 5 years of age. Data extracted from the books will include last menstrual period, number of ANC visits, treatment of medical conditions, ANC profile test results, mode of delivery, delivery outcomes, newborn health at delivery, birth weight and prevention interventions given (including insecticide treated bed nets, IPTp-SP, iron and folate supplements and Tetanus Toxoid vaccinations).

#### The community health promoter case report form

2.10.2

The trial designed a CHP CRF attached to the MCH books issued within the trial catchment area. It contains a section to be filled by CHPs during home visits to document the ANC and PNC-related services they offered and a section for ANC staff to comment and sign off on the information entered by CHPs. This will enable the mother to have a record of all services received during the antenatal and immediate postnatal period.

#### Participant interviews

2.10.3

Trial data clerks and fieldworkers will interview women at delivery and the 6–8-week postpartum period. Data collected will cover demographic details, socio-economic status, treatment of common conditions during pregnancy, place of delivery (health facility or home), type of delivery (vaginal or caesarean section), complications during delivery, the health of the baby at delivery, lactation history, use of prevention interventions (such as bed nets, malaria chemoprophylaxis, and iron and folate supplements), care-seeking behaviour, past obstetric history and access to care.

#### Healthcare facility registers

2.10.4

Trial data clerks and fieldworkers will abstract participant data from other clinic and ward registers to corroborate participant interviews and data missing from MCH books. These data include pregnancy outcomes, complications at delivery and other newborn morbidity outcomes. These registers include maternity, adult ward, gynaecology ward, out-patient department and child welfare clinic registers.

### Data capture, storage and curation

2.11

Data clerks will enter de-identified participant data on REDCap using internet-enabled tablets for encrypted data transfer to a secure, shared drive managed by Kenya Medical Research Institute (KEMRI) and backed up on a secure server at LSTM, UK. They will maintain a separate participant link log with participant identifiers accessible to the data clerks and data manager for query resolution.

Data validation will be completed by a data manager who will work with the trial statistician to develop syntax-driven consistency checks and data cleaning steps. Once cleaned and locked, the trial statistician will create final variables for analysis. The final cleaned database will be available in SAS, STATA and SPSS formats. A REDCap data dictionary of the raw database will be available, and the data dictionary of endpoints and other derived variables will be provided on request.

### Analytical plan/statistical methods

2.12

The intention-to-treat analysis population will consist of all eligible recruited participants who consented to participate in the trial from all randomised clusters. The per-protocol analysis populations will be those eligible, recruited and consented whose clusters had full implementation after WIT training on “analysing and using data to innovate” was completed within the expected timelines (Figure 2). These WITs will have determined a problem statement, developed a change plan, implemented it and tracked the relevant indicators in their monthly meetings.

No formal interim analysis will be carried out due to the long period between exposure to intervention and outcome ascertainment, and because this study does not test a direct patient-level intervention. The Institutional Review Boards (IRBs), the DMC and the Trial Steering Committee (TSC) will review study enrolment, progress and any safety concerns arising while the study is ongoing. Therefore, we will not define a stop criterion for this trial based on interim analyses. Instead, the trial will be stopped due to any major safety concerns, including direct harm to participants, as agreed upon by the IRBs, DMC and TSC.

We will conduct the primary analysis on the intention-to-treat population (ITT) using a binomial multilevel (random effects) model with a logit-link for estimation after which risk ratios (RR) and 95% confidence intervals will be estimated using parametric bootstrap procedures. This model was chosen as directly estimating RR is less robust, because RR may vary for reasons other than the magnitude of the effect because it is a ratio of two posterior probabilities, both of which are dependent on baseline prevalence of an outcome (22).

We will incorporate the facility (cluster) as a random effect and estimate *P*-values using parametric bootstrap procedures. We will assume the structure of the variance–covariance matrix for the random effect to be exchangeable. We will use similar methods of analysis to obtain crude and adjusted proportions for secondary outcomes and estimate standard errors of effect estimates while accounting for cluster-level correlation in all analyses.

Covariate analyses will be performed on the primary outcome on the ITT population, using baseline values: age (continuous, years), gravidae (paucigravidae (1st or 2nd), multigravidae (3rd+), education (primary not completed, primary, secondary, post-secondary) and marital status (single, married/co-habit, divorced/separated, widow). Pre-specified subgroup analyses will be performed for the primary outcome on the ITT population on stratification and baseline covariate variables, with age dichotomised into “lesser than” or “greater than” median. The treatment effect within each category of these variables will be estimated, and the interaction effect between treatment and each variable will be assessed to explore effect modification.

Missing baseline co-variables (as defined in the SAP prior to data lock) will be imputed using simple imputation methods based on the co-variable distributions, should the missing values for a particular co-variable be less than 5%. If the missing values for a covariable are ≥5%, then they will be imputed using Markov chain Monte Carlo (MCMC) methods. In the event of imputation for missing values used in primary or secondary outcome analyses, sensitivity analyses using complete cases will also be carried out.

We will not use imputation when missing outcome data arises due to incomplete data in MCH books and will report the fraction of missing outcome assessments by study arm for the intention-to-treat study population.

For secondary outcomes, confidence intervals and *P*-values will not be adjusted for multiple testing. However, care will be taken when interpreting the findings from these analyses. Subject to journal requirements, the following statement will be added to the figure or table notes comparing multiple secondary outcomes: “The *P*-values and widths of the confidence intervals have not been adjusted for multiplicity, so should not be used to infer definitive treatment effects for secondary outcomes.”

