### Cluster definition, randomisation and blinding

2.7

We will define a cluster as an ANC clinic meeting selection criterion, and this will be the unit of randomisation. An independent statistician will use a covariate-constrained randomisation approach to achieve balance across the two study arms. Specifically, we will apply the *l2* balance metric implemented in the “**cvrall**” package in R statistical software. All possible allocation schemes will be evaluated against predefined balance criteria, and a final allocation will be selected at random from a constrained set. A fixed random seed will be used to ensure reproducibility of the randomisation procedure. These covariates include sub-county, number of functional community units, number of CHPs, number of women of childbearing age, service provision level and the number of women attending four ANC visits and eight ANC visits.

We will convene the county and sub-county leadership, facility representatives and community representatives in a public event during which three County leaders will be asked to pick an unmarked sealed envelope containing details of allocation to a randomisation arm. We are unable to blind the allocation of arms given the nature of the intervention but will use a 5 km buffer zone between intervention and control facilities to minimise risk of contamination.

To minimise bias, we will use an objective primary outcome measure, and the statistician will be blinded regarding the allocation arm when the statistical analysis plan (SAP) is developed and analytical syntax is written. The actual allocation will only be provided to the statistician after locking the database and approval of the SAP by an independent Data Management Committee (DMC).

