#### Primary endpoint

2.8.1

The primary endpoint will be the proportion of pregnant women attaining at least eight ANC contacts defined as either a scheduled ANC visit in the facility or a scheduled ANC contact with a CHP in the community assessed at birth (or within the first 6–8 weeks for home births). Community ANC contacts will be defined as a home visit that covers the elements of a community ANC visit plus at least one diagnostic test or the distribution of at least one drug. Diagnostic tests or drugs administered include pregnancy tests, malaria tests, iron and folate supplements, sulphadoxine-pyrimethamine, co-trimoxazole and mebendazole.

During a baseline survey, we estimated 3% of the pregnant women in Homabay achieved eight ANC contacts and deemed an increase to 12% would be the minimum effect size to warrant national scale-up of the intervention. To detect this four-fold increase in the primary outcome assuming an intra-cluster correlation coefficient (ICC) of 0.025, 90% power and an alpha of 0.05, a sample size of 1,024 women in 16 clusters (8 per arm) would be required giving an average cluster size of 64 women. To account for efficiency loss due to cluster size imbalance, we increased clusters to 9 per arm resulting in a total of 1,152 participants. To adjust for anticipated 20% loss to follow-up, we increased the sample size estimate to 1,440 participants in total (720 per arm) giving an average cluster size of 80 women. The sample size calculation will be reviewed and updated (if necessary) after completion of baseline data collection from 1,620 participants in trial sites to obtain an updated ICC. Baseline data collection will take place in the months during which WIT training and embedding of the intervention will occur, prior to recruitment of the first patient-in (Figure 3).

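### The primary model as described omits every covariate used to constrain the randomisation; if those covariates are prognostic, the test is conservative and precision is forgone

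*Protocol article*

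**What the plan says.** Section 2.7 (Cluster definition, randomisation and blinding): "An independent statistician will use a covariate-constrained randomisation approach to achieve balance across the two study arms". The balancing variables are sub-county, the counts of community units, of CHPs and of women of childbearing age, the level of service, and the counts of women making four and eight ANC visits. All seven are cluster-level.

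Section 2.12 (Analytical plan/statistical methods) sets a logit-link multilevel model for the primary outcome, with risk ratios and P-values from a parametric bootstrap. On its terms it says: "We will incorporate the facility (cluster) as a random effect and estimate". No fixed effect beyond the implied arm effect is named. The same section adds: "Covariate analyses will be performed on the primary outcome on the ITT population, using baseline values: age (continuous, years"), followed by gravidity, education and marital status. These are individual-level, and none was used in the randomisation. Stratification variables reappear only as subgroups.

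Section 2.8.1 (Primary endpoint) gives the planning figures, and says that the sample size will be reviewed "after completion of baseline data collection from 1,620 participants in trial sites to obtain an updated ICC". No other use of that baseline round is stated.

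**The concern.** Constrained randomisation discards allocations in which the arms differ much on the chosen covariates. If those covariates predict the outcome, the arm difference varies less over the permitted allocations than over all allocations. A random-intercept model without the covariates still counts the variation they explain as between-cluster error. The parametric bootstrap does not repair this, because it simulates from the same fitted model, which carries no information about the constraint. P-values are then too large and intervals too wide.

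Between-cluster variation matters here. At ICC 0.025 and 64 women per cluster, its share of the variance of a cluster proportion is 64 × 0.025 / 2.575 = 62%. Earlier four- and eight-visit attendance is a plausible predictor of reaching eight contacts. At stake is precision that the design has already paid for.

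**Working it through.** **1. The plan's own figure.** Inputs from section 2.8.1: "we estimated 3% of the pregnant women in Homabay achieved eight ANC contacts"; the investigators "deemed an increase to 12% would be the minimum effect size to warrant national scale-up of the intervention"; "assuming an intra-cluster correlation coefficient (ICC) of 0.025, 90% power and an alpha of 0.05"; result "a sample size of 1,024 women in 16 clusters (8 per arm) would be required giving an average cluster size of 64 women".

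- Individually randomised n per arm, two-sided, pooled variance under the null: [1.96·√(2·0.075·0.925) + 1.2816·√(0.03·0.97 + 0.12·0.88)]² / 0.09² = (0.7301 + 0.4704)² / 0.0081 = 178.
- Design effect: 1 + 63 × 0.025 = 2.575. Then 178 × 2.575 = 458 per arm; 458/64 = 7.16, rounded up to 8 clusters; 8 × 2 × 64 = 1,024.
- 9 × 2 × 64 = 1,152, and 1,152/0.8 = 1,440. The stated figures reproduce.

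**2. Power without adjustment at the protocol's ICC.** With 9 clusters of 64 per arm, SE = √[2.575 × (0.0291 + 0.1056)/576] = 0.02454, and 0.09/0.02454 = 3.67. Power is 95.6% by the normal approximation and 93.1% by a noncentral t with 16 df. Both exceed 90%.

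**3. Effect of the constraint.** Simulation: 18 clusters of 64, seven balancing covariates, allocation drawn from the best 10% of all C(18,9) = 48,620 by the l2 score. One covariate, standing for earlier ANC uptake, explains a share R² of between-cluster variance on the logit scale. Type I error is at 5% in both arms; power is for 3% versus 12%. R², the logit SD and the 10% cut-off are assumptions; the article gives none of them. Adjusted means adjusted for that one covariate.

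Logit mixed model, with the likelihood-ratio cut-off calibrated under simple randomisation as a stand-in for the bootstrap (1,200 runs):

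| SD | R² | Type I unadj. | Type I adj. | Power unadj. | Power adj. |
|---|---|---|---|---|---|
| 0.6 | 0.3 | 0.023 | 0.043 | 0.956 | 0.979 |
| 0.6 | 0.6 | 0.034 | 0.049 | 0.976 | 0.998 |
| 0.9 | 0.3 | 0.034 | 0.041 | 0.788 | 0.846 |
| 0.9 | 0.6 | 0.021 | 0.048 | 0.816 | 0.950 |

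Cluster-level regression (2,500 runs):

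| SD | R² | Type I unadj. | Type I adj. | Power unadj. | Power adj. |
|---|---|---|---|---|---|
| 0.6 | 0.3 | 0.040 | 0.052 | 0.956 | 0.967 |
| 0.6 | 0.6 | 0.035 | 0.043 | 0.960 | 0.985 |
| 0.9 | 0 | 0.055 | 0.055 | 0.781 | 0.776 |
| 0.9 | 0.3 | 0.037 | 0.049 | 0.775 | 0.844 |
| 0.9 | 0.6 | 0.026 | 0.047 | 0.809 | 0.936 |

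The Monte Carlo SE of a 5% rate is √(0.05·0.95/1200) = 0.6 points and √(0.05·0.95/2500) = 0.4 points. A further cluster-level simulation of the same design gave about 1–4% unadjusted type I error and gains of 2–11 points. The summary ranges therefore run slightly wider than the tables.

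**4. Cost of adjusting.** With R² = 0, one covariate moves power from 0.947 to 0.940 (SD 0.6) and from 0.781 to 0.776 (SD 0.9). Adjusting for all seven is a different matter. At R² = 0, 0.3 and 0.6, power goes from 0.947, 0.956 and 0.960 to 0.862, 0.907 and 0.949 at SD 0.6, and from 0.781, 0.775 and 0.809 to 0.660, 0.740 and 0.865 at SD 0.9.

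**5. The baseline round as a covariate.** 1,620/18 = 90 women per cluster; at 3% that is 2.7 expected events. Reliability of a cluster's proportion at ICC 0.025 is 90 × 0.025/(1 + 89 × 0.025) = 0.70. Section 2.8.1 places this round in the months of WIT training and embedding, so it may also be affected by allocation.

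**The case against.** The strongest reply is that the article never calls the primary model unadjusted. It condenses a fuller plan, and an SAP approved by the DMC may add fixed effects. That stands as a limit on wording: the point concerns the model as described. It does not dispose of the point, because section 2.12 goes on to name covariates for the primary outcome and that list contains no design variable. Likewise, the article gives one use for the baseline round but does not exclude others.

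Second, the conservatism is conditional. A reader might infer that the P-values and intervals are wrong as such. The documents do not show how prognostic the constraint covariates are. Several are measures of facility size, and with R² = 0 the test stays near 5%. This stands.

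Third, a reader might infer that the trial is underpowered unless it adjusts, since unadjusted power at SD 0.9 is about 78–82%. The protocol's own figures do not support this. Under a logit-normal cluster effect, ICC 0.025 corresponds to an SD of about 0.83 at a rate of 3% and 0.58 at 7.5%, so SD 0.9 is more clustering than planned at either rate. Section 2.8.1 does not say at which rate its ICC applies. At that ICC on the proportion scale, power is 93–96% unadjusted.

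Fourth, adjustment is not free with 18 clusters. This holds for the full set of seven, but hardly for one or two terms.

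**Conclusion.** The concern holds as a mismatch between design and analysis: seven cluster-level variables constrain the allocation, and none enters the primary model or covariate analyses as described. To the extent that they predict the outcome, the test and its bootstrap are conservative, at about 1–4% instead of 5% for an assumed R² of 0.3–0.6 and a best-10% constraint. One-covariate adjustment brings type I error back to about 4–5% and adds about 2 points of power at logit SD 0.6, or about 4–13 points at SD 0.9. The error is in the safe direction, vanishes if the covariates are uninformative, and leaves the planned 90% power intact at ICC 0.025. It is precision forgone, not a shortfall and not an invalid test.

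**What to change.** Before unblinding and database lock, state in the SAP that the primary model adjusts for one or two named cluster-level constraint covariates, in the form used for the randomisation. The first choice is pre-randomisation four- or eight-visit ANC uptake, scaled by a pre-randomisation denominator if one is held (the article lists counts). The second is service level. Keep the unadjusted model as a sensitivity analysis.

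Do not adjust for all seven. Do not use the 1,620-woman baseline round as the adjuster unless it is restricted to women whose pregnancies ended before any WIT activity. The end of training in April 2024 (section 4.2) is not a clean cut-off, because section 2.5.1 has WITs already working with facility staff, CHPs and communities between the training sessions. Any permutation test should permute only within the constrained set.

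Cost: SAP wording and one or two of about 16 cluster degrees of freedom, or about one point of power if the covariate is uninformative. Variables used as they stood at randomisation need no new data collection.

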### Public and stakeholder involvement

2.13

The trial was co-developed with the MoH (Division of Reproductive Health and Division of Community Health) and County government health administration. We collectively chose the primary outcome (eight ANC contacts) based on changes in national policy (4) and agreed on the definition of community ANC contacts and the design of the CHP CRF. We selected the electronic data capture tools (eCHIS and KenyaEMR) in line with MoH priorities for national scale-up. County and sub-county administration members will form part of the team training ANC staff and CHPs in trial sites and offering support supervision to WITs in intervention sites. County and sub-county leadership, facility representatives and community representatives will be present during allocation of clusters to intervention/control arm.

## Ethics, oversight and dissemination

3

The trial will be conducted in compliance with the principles of the Declaration of Helsinki (1996), the principles of Good Clinical Practice and in accordance with regulatory requirements in Kenya. Trial staff will explain the trial's purpose to each potential participant and clearly communicate that participation is voluntary and will not affect their access to services at the facility before participants are asked for signed informed consent. Participants unable to read and write will be requested to provide oral consent and a thumbprint in the presence of an impartial witness. Women aged below 18 years who are pregnant or have children are considered “mature minors” in Kenya and will be able to consent per KEMRI-Scientific and Ethics Review Unit guidelines.

A TSC will provide overall oversight and will comprise of at least 75% independent members. They will advise on all aspects of the trial, monitor progress, adherence to protocols and ethics, and agree on any substantive protocol amendments. They will ensure patients' rights, safety and well-being are upheld and align with the safeguarding approach. A DMC consisting of four independent members (a chair, a topic expert, an obstetrician and a biostatistician) will periodically review and evaluate the accumulated study data for participant safety, study conduct, progress and efficacy and give recommendations to the investigators. The DMC will also review and approve the statistical analysis plan which will be implemented by the trial statistician. Trial results will be published in peer-reviewed journals with equitable authorship governed by International Committee of Medical Journal Editors criteria. Study staff will present results during community meetings in the trial sites and in conferences.

## Discussion

4

The C-it-Du-it trial will provide evidence on the impact of community QI interventions using digitally linked community and facility data in a real-world health systems context. The push to digitise patient data at the facility and community levels has the potential to improve patient outcomes through improved data quality and data access, enabling the tracking of individual pregnant women. While donors and governments rush to digitise and link health data, we do not currently know if digital data linkage alone will work to achieve health outcomes or if linkage plus structured community data use is necessary.

Previous studies linking ANC data in LMICs have shown QI methodologies are rarely adapted for use beyond traditional healthcare facilities with limited implementation in resource-poor settings (23). In this study, we have worked with nationally adopted EMR systems at community and facility levels, added bidirectional eCHIS–EMR linkage, adapted QI training to community teams, developed community dashboards and included a focus on adolescents. We anticipate a causal pathway to increased ANC uptake. In our case, the data linkage should give more visibility of missed/late pregnancies leading to targeted CHP follow-up and increased ANC uptake. WITs can work together to identify problems from the data (such as late presentation among adolescents), investigate the root cause (e.g., school dropout, stigma, etc.), develop a targeted intervention (e.g., with schools, families and communities) and efficiently monitor progress on that metric.

